| Blood (EDTA) host genome (host DNA) j                           |                 | X        |                                                  |                               |                               |                                           |                                              |
| Mid-turbinate nasal swab viral genome j                         |                 | X        |                                                  |                               |                               |                                           |                                              |

EDTA=ethylenediaminetetraacetic acid; FiO2=fraction of inspired oxygen; PBMC=peripheral blood mononuclear cell; PCR=polymerase chain reaction;

PO2=partial pressure of oxygen; RT PCR=reverse transcription polymerase chain reaction; SARS-CoV-2= severe acute respiratory syndrome coronavirus 2;

SoC=standard of care; SpO2=oxygen saturation; SST=serum separator tube.

Note: Additional assessments, if required, will be defined in the sub-protocol.

a These visits will be performed even if a patient has already been discharged. If discharged prior to scheduled visit, in-person visits are preferred, but recognising that quarantine and other factors may limit the patient's ability to return to the clinic, these visits may be conducted by telephone or with a home visit by study staff. For visits conducted by telephone, it will not be possible to perform some scheduled assessments (eg, vital signs). The Day 29 assessments will also be performed, where possible, for patients who discontinue the study prematurely.

b Medical history includes estimated date and time of first symptoms and number of co-morbidities (eg, respiratory, cardiovascular, metabolic, malignancy, endocrine, gastrointestinal, immunologic, renal).

c Baseline assessments should be performed prior to study drug administration.

d Includes ordinal score, National Early Warning Score 2 (NEWS2), oxygen requirement, noninvasive or invasive ventilator requirement, including start and stop of low- or high-flow oxygen supply or of any form of ventilation etc.

e If done as part of SoC, blood gases results to be fully recorded with date and time.

f For parameters, see [Table 5](#).

g Laboratory tests performed in the 48 hours prior to enrolment will be accepted for determination of eligibility.

h Any laboratory tests performed as part of routine clinical care within the specified visit window can be used for safety laboratory testing.

i Samples collected for immediate laboratory processing and frozen storage.

j Samples collected dependent on capacity of study centre, need for reduced study burden on staff, and potentially limited access to patients.

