| Targeted physical examination (focused on lung auscultation)                                       |                    |                        | X                                 |                                  |                                  |                                                 |                                                    |
| Vital signs, including temperature, pulse rate, blood pressure, respiratory rate, SpO 2 |                    | X c         | X                                 | X                                | X                                |                                                 |                                                    |

|                                                                                                                               | Screening       | Baseline         |                                                  |                               |                               |                                           |                                              |
|-------------------------------------------------------------------------------------------------------------------------------|-----------------|------------------|--------------------------------------------------|-------------------------------|-------------------------------|-------------------------------------------|----------------------------------------------|
| Day (± Window)                                                                                                                | Day -1 or Day 1 | Day 1            | Daily Until Hospital Discharge                   | Day 15 a (±2 days) | Day 29 a (±3 days) | Day 60 a (±4 days) (Follow-up) | Day 90 a (±6 days) (End of Study) |
| Clinical assessments d                                                                                             |                 | X c   | X                                                | X                             | X                             |                                           |                                              |

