| Targeted medication review (including use of vasopressors)                                                                    |                 | X c   | X                                                | X                             | X                             |                                           |                                              |
| Adverse event evaluation                                                                                                      |                 | X                | X                                                | X                             | X                             | X                                         | X                                            |
| Disease-related co-infection evaluation (including microbiologic/infectious agent assessment/results; bacteria, viral, fungi) |                 | X                | X                                                |                               |                               |                                           |                                              |
| Survival status                                                                                                               |                 | X                | X                                                | X                             | X                             | X                                         | X                                            |
| Blood gases and FiO 2 at worst PO 2 e                                                        | X               | X                | X                                                | X                             |                               |                                           |                                              |
| SAFETY LABORATORY                                                                                                             |                 |                  |                                                  |                               |                               |                                           |                                              |

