- **Stage 2** of the study (confirmation) is intended to provide confirmatory data of the identified candidate agents from Stage 1, to fully evaluate disease outcomes, including severe AEs, overall AEs, disease-related co-infection complications (eg, pneumonia, septic shock), and overall mortality in an expansion stage. Patients and outcomes from Stage 1 will not form part of Stage 2.

Some candidate agents will still be in Stage 1 of the study at the point where other candidate agents have progressed to Stage 2.

Patients will be randomised to receive one of the candidate agents that is being evaluated at the time of randomisation and whose inclusion/exclusion criteria they meet (as an add-on to SoC) or to a control arm where only SoC is administered.

In each stage of the study, patients will be screened on Day -1 or Day 1, and will remain in the clinic from Day 1 until fit for discharge. Dosing with the candidate agent (as an add-on to SoC) will commence on Day 1. The last day of assessments while hospitalised will be on Day 29. An outpatient visit will be conducted on Day 60 ( $\pm 4$  days), with an end-of-study visit conducted on Day 90 ( $\pm 6$  days).

Enrolment of patients will be continuous throughout the study for each candidate agent until the total randomisation number of planned patients for Stage 1 and Stage 2 is achieved. Enrolment under a sub-protocol for a specific candidate agent may also be stopped in the event of success or failure of the candidate agent. The Master Protocol will continue enrolling patients as long as there are candidate agents that are enrolling. It is estimated that up to 1800 patients will participate in the overall study.

Study centres will be located in the United Kingdom. Overall, it is estimated that approximately 18 centres and investigators will initially take part in the study.

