### **8.4.1 Time Period and Frequency for Collecting AE and SAE Information**

All AEs will be collected from provision of informed consent until the final follow-up visit, at the time points specified in the SoA (Section 1.3).

All SAEs will be recorded and reported to the Sponsor or designee within 24 hours, as indicated in [Appendix 4](#). The Investigator will submit any updated SAE data to the Sponsor within 24 hours of it being available.

Investigators are not obligated to actively seek AEs or SAEs after conclusion of the study participation. However, if the Investigator learns of any SAE, including a death, at any time after a patient has been discharged from the study, and he/she considers the event to be reasonably

related to the study treatment or study participation, the Investigator must promptly notify the Sponsor.

The method of recording, evaluating, and assessing causality of AEs and SAEs and the procedures for completing and transmitting SAE reports are provided in [Appendix 4](#).

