#### **8.4.7 Disease-Related Events and/or Disease-Related Outcomes Not Qualifying as Adverse Events or Serious Adverse Events**

Events that are typically associated with the disease under study will not be reported according to the standard process for expedited reporting of SAEs even though the event may meet the definition of an SAE.

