|------------------------------------------------------------------------------------------------------------------------------------------------------------------------------------------------------------------------------------------------------------------------------------------------------------------------------------------------------------------------------------------------------------------------------------------------------------------------------------------------------------------------------------------------------------------------------------------------------------------------------------------------------------------------------------------------------------------------------------------------------------------------------------------------------------------------------------------------------------------------------------------------------------------|
| 
 
Any clinically significant abnormal laboratory findings or other abnormal safety assessments which are associated with the underlying disease, unless judged by the Investigator to be more severe than expected for the patient's condition.
 
The disease/disorder being studied or expected progression, signs, or symptoms of the disease/disorder being studied, unless more severe than expected for the patient's condition.
 
Medical or surgical procedure (eg, endoscopy, appendectomy): the condition that leads to the procedure is the AE.
 
Situations in which an untoward medical occurrence did not occur (social and/or convenience admission to a hospital).
 
Anticipated day-to-day fluctuations of pre-existing disease(s) or condition(s) present or detected at the start of the study that do not worsen.
 
 |

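### The dedicated co-infection evaluation stops at hospital discharge, although Stage 2 is meant to evaluate co-infection fully, so systematic ascertainment ends sooner in an arm that is discharged sooner

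*Protocol*

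**What the plan says.** **The schedule.** In the Protocol's Section 1.3, the row "Disease-related co-infection evaluation (including microbiologic/infectious agent assessment/results; bacteria, viral, fungi") carries a mark at Baseline and in the column headed "Daily Until Hospital Discharge". It is blank at Days 15, 29, 60 and 90. Neighbouring rows go further: vital signs, clinical assessments and the targeted medication review to Day 29, and adverse event evaluation and survival status to Day 90.

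**Later contacts.** Note a to the schedule says of the Day 15, 29, 60 and 90 visits: "These visits will be performed even if a patient has already been discharged". They may be held by telephone or as a home visit.

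**The Stage 2 aim.** Section 4.1, like the synopsis, says that Stage 2 is intended "to fully evaluate disease outcomes, including severe AEs, overall AEs, disease-related co-infection complications (eg, pneumonia, septic shock), and overall mortality in an expansion stage".

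**The adverse event route.** Section 8.4.1 states: "All AEs will be collected from provision of informed consent until the final follow-up visit". The list in Appendix 4 of what is not an adverse event includes "The disease/disorder being studied or expected progression, signs, or symptoms of the disease/disorder being studied", unless more severe than expected for the patient. Appendix 4 adds that what is not an adverse event cannot be a serious one. Section 6.3 states that the study is not blinded.

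**Who follows the schedule.** Under Section 8.0, the arm on standard of care (SoC) alone follows this example schedule, and candidate arms follow the schedule in their sub-protocol.

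**The concern.** Stage 2 lists co-infection as an outcome in its own right, but the only row that looks for it systematically, with microbiology, ends at discharge. Live discharge, or fitness for it, is a component of the primary endpoint, so an effective agent shortens the period in which the row is active. With equal true infection rates, a comparison of counts from this row alone would tend to favour the arm that leaves hospital earlier.

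The gap also matters for safety. The protocol names immunomodulatory agents among the possible candidates, and infections that appear after discharge are of interest for that class. The contacts at which they could be asked about already exist; only the item is missing.

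**Working it through.** **1. Check the effect assumptions.** Section 9.3 gives response by Day 29 of 70% on SoC and 85.5% on a candidate agent, and a hazard ratio of 1.6. With exponential times, the two rates imply a hazard ratio of ln(0.145)/ln(0.30) = 1.604. The events needed are 4(z_α + z_β)²/(ln HR)².

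| Stage | One-sided alpha, power | HR 1.6 | HR 1.604 | Protocol |
|---|---|---|---|---|
| 1 | 0.10, 80% | 82 | about 81 | 81 |
| 2 | 0.025, 90% | 191 | about 188 | 188 |

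The protocol's figures reproduce, so its rates can be used below.

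**2. Days covered by the co-infection row.** Assume that response equals discharge, that times are exponential over 28 days, and that nobody dies. The daily discharge hazard is λ = −ln(1 − p)/28, and the mean number of covered days is p/λ.

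- SoC: λ = −ln(0.30)/28 = 0.0430, so 0.70/0.0430 = 16.3 days (58% of 28).
- Candidate: λ = −ln(0.145)/28 = 0.0690, so 0.855/0.0690 = 12.4 days (44% of 28).
- Difference 3.9 days; ratio 12.4/16.3 = 0.76.

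**3. What this could do to recorded incidence.** The documents give no infection rate, so take an assumed constant daily hazard g, equal in both arms and the same before and after discharge. The proportion recorded by the row alone is g/(g + λ) × [1 − exp(−28(g + λ))]. Full 28-day ascertainment gives 1 − exp(−28g) in either arm.

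| g per day | SoC | Candidate | Ratio | Full 28 days, both arms |
|---|---|---|---|---|
| 0.25% | 4.0% | 3.0% | 0.76 | 6.8% |
| 0.5% | 7.7% | 5.9% | 0.77 | 13.1% |
| 1% | 14.6% | 11.3% | 0.77 | 24.4% |
| 2% | 26.3% | 20.6% | 0.78 | 42.9% |

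With 126 patients per arm and no true effect, the chance of a difference at two-sided 0.05 runs from about 6% to 19% over this range.

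**4. Relax response equals discharge.** Section 8.1.1 counts Grade 5 to Grade 3 as a response, and that patient is still in hospital. If discharge followed response by d days (an assumption), the covered days are d + [1 − exp(−λ(28 − d))]/λ.

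- d = 2: 17.7 versus 14.1 days, ratio 0.80.
- d = 5: 19.6 versus 16.5 days, ratio 0.84.

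Capture of later infections as adverse events would bring the ratio of recorded infections closer to 1.

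**The case against.** **Infections can be recorded after discharge.** A reader might infer from the row that they cannot. The documents do not support that. Adverse events are collected in every arm to the final follow-up visit, with evaluation marked at Days 15, 29, 60 and 90. A new pneumonia or septic shock that meets the definition is captured, as a serious event if it is life-threatening or leads to admission. Section 6.5 also has medication during the study recorded with its reason for use. This stands. What is lost is the systematic, microbiology-based evaluation.

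**Section 8.4.7 does not close the adverse event route.** Its heading is broad, but the text says only this: "Events that are typically associated with the disease under study will not be reported according to the standard process for expedited reporting of SAEs". That limits expedited reporting, not recording. The exclusion in Appendix 4 is the better support for calling the route narrower, and whether it reaches a separate bacterial or fungal infection is arguable. The uncertainty remains, because the protocol itself calls these complications disease-related and leaves the decision to an unblinded investigator.

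**No biased test is specified.** Co-infection is not an endpoint in Table 1 and has no between-arm test in Table 4 or analysis in Section 9.5.2. It would therefore be too strong to say that the plan credits a faster-discharging agent by construction.

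**Part of a difference may be real.** Fewer hospital days may mean fewer hospital-acquired infections. If infection is rarer after discharge, the distortion shrinks.

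**Stopping at discharge is coherent, and sub-protocols can add items.** Microbiology cannot be done by telephone, other inpatient rows also stop, and events of special interest are set for each agent. But a sub-protocol that extended this row for a candidate arm alone would leave the SoC arm on the shorter schedule and reverse the imbalance.

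**Conclusion.** The point holds as a mismatch between the stated Stage 2 aim and the schedule. Dedicated co-infection ascertainment ends at an event that treatment is meant to bring forward, while the remaining route is narrower and partly a matter of open-label judgement.

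The ratio of 0.76 (16.3 versus 12.4 covered days) is an upper-end illustration. It rests on response taken as discharge, an equal and constant infection hazard, no deaths and no capture after discharge. The first is at odds with the protocol's own example of a responder, and the last with its adverse event collection, so the true distortion would be smaller. It should not be read as a demonstrated bias in a planned analysis. The primary endpoint and the sample size are unaffected. This is a cheap improvement, not an error that threatens the trial.

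**What to change.** In the Master Protocol schedule, mark the co-infection row at the existing Day 15 and Day 29 contacts for all arms. Ask about any infection diagnosed or treated since the last contact, and record its date and any microbiology results that are available. Making the change in the Master Protocol keeps the SoC arm and the candidate arms on the same footing.

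Summarise co-infection as cumulative incidence to Day 29 in all randomised patients, with death as a competing event. Each surviving patient who is followed up then contributes the same 28 days, whatever the date of discharge.

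The cost is one item at two contacts that already take place. The drawback is that infections after discharge are patient-reported when the contact is by telephone. If the sponsor prefers not to extend the row, the protocol should state that co-infection is compared over a fixed window from adverse event data, and the Stage 2 aim should be worded to match.

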## **2.0 INTRODUCTION**

### **2.1 Study Rationale**

There are currently no approved therapeutic agents available to treat coronaviruses such as severe acute respiratory syndrome coronavirus 2 (SARS-CoV-2), the causative agent of COVID-19 disease, and there is an urgent public health need for rapid development of such interventions. This adaptive platform study is designed to rapidly assess multiple candidate agents as treatments for COVID-19. Candidate drugs that are initially assessed as being efficacious will be moved from an evaluation (pilot) stage to a confirmatory stage, with candidate agents being added to and removed from the study on an ongoing basis, depending on the results of their evaluation. Patients to be included in the study will be hospitalised and may require either supplemental oxygen, noninvasive ventilation or high-flow oxygen devices.

### **2.2 Background**

Coronaviruses are single-stranded RNA viruses, capable of causing life-threatening disease in humans and animals. The novel coronavirus SARS-CoV-2 was initially identified during an outbreak of viral pneumonia cases of unknown cause in China. Most of the initial infections outside of China were travel associated (ie, from people who had travelled from the infected regions of China to other countries), although person-to-person transmission in other countries was quickly established. The disease caused by the SARS-CoV-2 virus has been designated COVID-19.

SARS-CoV-2 binds via the angiotensin-converting enzyme (ACE) receptor located on alveolar cells and intestinal epithelia. The virus is mutating, indicating that virulence and transmission will shift over time, and showing diversity in critical surface protein. New evidence suggests there are 2 groups of SARS-CoV-2; L-type and S-type. S-type is the less aggressive (30%); the L-type is now the most prevalent version (70%) and is more aggressive. Additionally, individuals appear to be affected to different degree with varying symptoms and outcomes. These findings strongly support an urgent need for immediate comprehensive studies and robust validation of testing methods that combine genomic data, chart records and clinical symptoms, to help better understand the disease, enable risk assessment, triage and support public health resource planning.

Due to the rapid global widespread of SARS-CoV-2, there is an urgent need to develop efficacious treatments for the disease. Current clinical studies involve the use of already approved medications for other indications (repurposing) where it is thought that they might also be effective in the treatment of COVID-19 disease, as well as development of antibody-based therapies against the virus.

This platform study will test multiple candidate agents, with the aim of identifying potentially efficacious treatments in the shortest timeframe possible. In addition, it will support secondary research objectives that are critical for understanding the disease, spread of infection and robust tests to track it.

### **2.3 Benefit/Risk Assessment**

There are currently no approved therapeutic agents available to treat coronaviruses such as SARS-CoV-2, and so while there may not be benefits for an individual patient participating in this study, there may be benefits to society if a safe and efficacious therapeutic agent can be identified during the global COVID-19 outbreak.

Detailed information about the known and expected risks and reasonably expected adverse events (AEs) of each candidate agent may be found in the corresponding sub-protocol for that agent.

